### Clinical experience

Clinical experience with olaparib is fully described in the current version of the olaparib IB.

## Research hypothesis

Olaparib administered as monotherapy in the maintenance setting improves progression free survival compared to placebo in patients with relapsed ovarian cancer who have a complete or partial response to platinum-based chemotherapy.

## Rationale for study design and doses

Based on the results of a pivotal phase II trial (D0810C00019), described in more detail below, olaparib as the capsule formulation at a daily recommended dose of 400mg twice daily (a total daily dose of 800mg) has been approved in EU as monotherapy for the maintenance treatment of adult patients with platinum sensitive relapsed (PSR) *BRCA* mutated (germline and/or somatic) high grade epithelial ovarian, fallopian tube, or primary peritoneal cancer who are in response (complete response or partial response) to platinum-based chemotherapy. In this phase II trial, Olaparib as maintenance treatment significantly improved progression-free survival among patients with platinum-sensitive, relapsed, high-grade serous ovarian cancer, not limited to *BRCA*m population.

The phase II study D0810C00019 is a randomised, double-blind, placebo-controlled study to evaluate maintenance treatment with olaparib (capsule formulation) in patients with platinum-sensitive relapsed high grade epithelial ovarian cancer who had received ≥2 previous platinum regimens and were in partial or complete response following their last platinum-containing regimen. The primary endpoint was investigator-assessed PFS. In total, 265 patients were randomised to olaparib 400 mg bid (136) or placebo (129). The primary analysis was carried out following 153 PFS events and demonstrated that maintenance treatment with olaparib led to a significant PFS improvement vs placebo [hazard ratio (HR) 0.35 (95% confidence interval (CI) 0.25 -0.49); median: 8.4 vs 4.8 months; p<0.00001] (Ledermann et al 2012). A subgroup analysis (pre-specified in the [SAP]) suggested that olaparib may lead to a greater clinical benefit in patients with a known germline *BRCA*m. g*BRCA*m status was determined retrospectively for all consenting patients (n=166) using blood samples taken before randomisation. s*BRCA*m status was determined from archival tumour samples of 196 patients. Since g*BRCA*wt patients may develop somatic tumour *BRCA* mutations, efficacy analyses were performed by known g*BRCA* mutation status and known total *BRCA* mutation status. g*BRCA*m patients had the greatest PFS benefit with olaparib maintenance vs placebo (HR, 0.17; 95% CI 0.09-0.31; median: 11.2 vs 4.1 months; P<0.001). The PFS benefit was consistent when s*BRCA*m patients were included to include an overall of 136 patients with *BRCA*m disease (HR, 0.18; 95% CI 0.11-0.31; median: 11.2 vs 4.3 months; P<0.0001). In an updated analysis (Ledermann et al 2016), an OS (77% maturity) advantage was seen with maintenance olaparib versus placebo in all patients (HR 0.73 [95% CI 0.55–0.96]; median overall survival was 29.8 months [95% CI 26.9–35.7] for those treated with olaparib vs 27.8 months [24.9–33.7] for those treated with placebo), and in patients with *BRCA*m (HR 0.62 [95% CI 0.41–0.94]; 34.9 months [95% CI 29.2–54.6] vs 30.2 months [23.1–40.7]). 11 (15%) of 74 patients with *BRCA*m received maintenance olaparib for 5 years or more. OS nominal p=0.025, which did not meet the required threshold for statistical significance [p<0・0095], however 30% g*BRCA*m placebo patients received a subsequent PARP inhibitor, confounding the OS data in this subgroup. Olaparib tolerability was similar in *BRCA*m patients and the overall population.

The phase II study D0810C000019 demonstrated the efficacy of olaparib maintenance when using the capsule formulation (8 capsules twice daily). A more patient friendly tablet formulation (2 tablets twice daily) has been developed. Study D0816C00002 (SOLO2) was a Phase III randomised, double-blind, placebo-controlled study of olaparib 300 mg bd (tablet formulation) as maintenance therapy in high grade ovarian cancer patients who were in response to their most recent platinum-based chemotherapy after ≥2 lines of treatment and who had a deleterious or suspected deleterious g*BRCA*m. The phase III confirmatory trial is conducted with the new tablet formulation. Results from the trial demonstrate a clinically-meaningful and statistically-significant improvement of progression-free survival (PFS) among patients treated with Lynparza compared to placebo and provide additional evidence to support the potential use of Lynparza in this patient population. Olaparib achieved a highly statistically significant and clinically meaningful prolongation in PFS compared with placebo, by Investigator assessment (HR, 0.30; 95% CI 0.22-0.41; median: 19.1 vs 5.5 months; P<0.0001); BICR assessment of PFS (HR, 0.25; 95% CI 0.18-0.35; median: 30.2 vs 5.5 months; P<0.0001) confirmed these results.

Further information is provided in the IB.

The current study will allow patients to complete their platinum-containing regimen prior to enrolment and then initiate maintenance treatment with olaparib. This study is to explore the use of Olaparib as maintenance monotherapy in PSR patients and to provide valuable further insight into patients’ benefit and tolerability.

For the current study, it is expected that participating patients may know their *BRCA* and HRR status after enrolment and will have undergone counselling in accordance with local hospital practice.

## Benefit/risk and ethical assessment

Olaparib is considered to have a positive benefit-risk profile in this study target population of relapsed platinum sensitive ovarian cancer patients based on the randomised phase II data in the same patient population demonstrating a significant and clinically meaningful prolongation of progression free survival, with an acceptable tolerability profile for use in the maintenance setting. Platinum-containing therapy is considered the treatment of choice for patients with recurrent platinum sensitive ovarian cancer, however the duration of response (DoR) and the prolongation of the progression free interval are usually brief and these chemotherapy regimens cannot be continued until progression as they are associated with neurological, renal and haematological toxicity and cannot generally be tolerated for more than about 6 cycles. Since chemotherapy is not a viable treatment option in the maintenance setting, there is a need for a maintenance treatment (following completion of chemotherapy) with adequate tolerance profile that can be taken until disease progression to extend the progression free interval in this patient population.

The current study design will allow patients to complete their platinum-containing regimen as per normal clinical practice prior to enrolment. The use of olaparib as a maintenance therapy after completion of chemotherapy may provide further benefit to patients in terms of prolongation of the progression free interval, increasing the interval between lines of chemotherapy, delaying further hospitalisation and the cumulative toxicities associated with chemotherapy. The tablet formulation is considered to be a more patient friendly formulation for long term use requiring patients to take up to 2 tablets twice daily as compared to the capsule formulation requiring 8 capsules twice daily. Considering that ovarian cancer is the leading cause of death from gynaecological tumours in the world, the clinically meaningful efficacy benefit of olaparib in the *BRCA* mutated and PSR patient population and the known tolerability profile of olaparib monotherapy, the current study is considered to have a positive benefit-risk profile. The known risks to olaparib monotherapy in terms of safety and tolerability are considered justifiable. Refer to the current IB for a complete description of the safety and tolerability profile.

## Study Design

This is a prospective, open-label, single arm, multi-centre interventional study to assess the clinical efficacy and safety of olaparib maintenance monotherapy as the tablet formulation in PSR high grade (serous or endometrioid) epithelial ovarian cancer patients (including patients with primary peritoneal and / or fallopian tube cancer).

Figure 1 Study Flow Chart

Notes: OC ovarian cancer; PR partial response; CR complete response; PFS progression free survival; PFS2 time to second progression; TFST time to first subsequent treatment; TSST time to second subsequent treatment; OS overall survival; TDT time to discontinuation of treatment;

Patients will be assigned to olaparib tablets p.o. 300 mg twice daily. They should initiate olaparib treatment within 8 weeks after their last dose of chemotherapy (last dose is the day of the last infusion).

Patients must have clinical and objective radiological tumour assessments according to RECIST 1.1 criteria at baseline and every 12 weeks relative to date of enrolment, until objective radiological disease progression as determined by the investigator. Patients could continue to receive olaparib for as long as determined by the investigator, until objective radiological disease progression or as long as in the investigator’s opinion they are benefiting from treatment in relation to other clinical assessments and they do not meet any other discontinuation criteria.

Once a patient has discontinued olaparib she will be managed as per local clinical practice but will remain in the study and data will be collected on subsequent treatments, progression and survival.

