**Figure 1 Study Flow Chart**

Notes: OC ovarian cancer; PR partial response; CR complete response; PFS progression free survival; PFS2 time to second progression; TFST time to first subsequent treatment; TSST time to second subsequent treatment; OS overall survival; TDT time to discontinuation of treatment;

Patients will be assigned olaparib tablets p.o. 300 mg twice daily. They should initiate olaparib treatment within 8 weeks after their last dose of platinum-containing chemotherapy (last dose is the day of the last infusion).

Patients must have clinical and objective radiological tumour assessments according to Response Evaluation Criteria in Solid Tumors (RECIST 1.1) criteria at baseline and every 12 weeks relative to date of enrolment, until objective radiological disease progression as determined by the investigator. Patients could continue to receive olaparib for as long as determined by the investigator, until objective radiological disease progression or as long as in the investigator’s opinion they are benefiting from treatment in relation to other clinical assessments and they do not meet any other discontinuation criteria. Once a patient has discontinued olaparib she will be managed as per local clinical practice but will remain in the study and data will be collected on subsequent treatments, progression, overall survival and safety.

Objectives

| **Primary Objective:** | **Outcome Measure:** |
| --- | --- |
| To assess the efficacy of olaparib maintenance monotherapy by investigator assessed progression free survival (PFS) according to RECIST 1.1 criteria. | Time from first dosing date of olaparib to date of disease progression or death from any cause (if this occurs before disease progression) |

| **Secondary Objective:** | **Outcome Measure:** |
| --- | --- |
| To assess the efficacy of olaparib maintenance monotherapy of *BRCA*m population by investigator assessed progression free survival (PFS) according to RECIST 1.1 criteria. | Time from first dosing date of olaparib to date of disease progression or death from any cause (if this occurs before disease progression) in BRCAm population |

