^d^ Safety blood samples do not need to be repeated on Day 1 of study treatment if assessed at least 3 weeks after the last dose of chemotherapy but within 7 days before starting study treatment, unless the investigator believes that it is likely to have changed significantly. Coagulation test should be performed at screening and if clinically indicated. For a list of all required laboratory tests please refer to Section [5.2.1](#_Laboratory_safety_assessments).

^e^ Pregnancy tests on blood or urine samples will be performed for women of childbearing potential within 28 days prior to the start of study treatment, on Day 1 of the study prior to commencing treatment, at the time points shown in Table 2 during study treatment and at the 30 day follow up visit If results are positive the patient is ineligible/must be discontinued from study treatment immediately.

^f^ Follow-up very 12 weeks after start of treatment until objective disease progression as defined by RECIST 1.1, up to 72 weeks, then every 24 weeks relative to date of enrolment. Any other sites at which new disease is suspected should also be appropriately imaged. If an unscheduled assessment was performed and the patient has not progressed, every attempt should be made to perform the subsequent assessments at their scheduled visits.

^g^ All ongoing adverse events/serious adverse events (AEs/SAEs) and any new AEs/SAEs identified during the 30 calendar days follow up period after last dose of study medication must be followed to resolution.

^h^ Sufficient study treatment should be dispensed for at least each treatment period plus overage.

^i^ All anti-cancer treatments (including, but not limited to, chemotherapy and targeted agents), and the investigators opinion of response to them plus the date of progression, post discontinuation of study treatment need to be recorded.

^j^ Only patients on treatment post progression are required to undergo this procedure.

^K^ Patients on treatment post progression are only required to undergo these procedures.

| Table 3 Study Schedule –Follow up Post Discontinuation of Study Treatment | | |
| --- | --- | --- |

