| Visit Number | **Off treatment follow up**  **Study treatment discontinued due to reasons other than disease progression**  **Visits every 12 weeks Follow up for 1st progression Tumour assessment visits every 12**  weeks or 24 weeksa | **Time to second progression (PFS2) and Survival for:**  • Patients who have discontinued study treatment due to disease progression  • Patients who have progressed off treatment  • Patients who were on study treatment post progression and / or after primary (PFS) analysis who subsequently discontinued study treatment  Every 12 weeks post discontinuation of study treatment |
| Visit Window | ±7d | ±7d |
| Blood sample for disease specific marker (CA-125) | X |  |
| Tumour Assessment (CT or MRI according to modified RECIST v1.1) a | X |  |
| Adverse Events | X | X |
| ECOG performance status | X | X |
| Subsequent cancer therapy following discontinuation of study treatment ^b^ | X | X |
| Time to second progression |  | X |
| Survival ^cd^ | X | X |

a RECIST follow-up assessments will be performed every 12 weeks (±1 week), up to 72 weeks, then every 24 weeks (±1 week) relative to date of enrolment. Follow-up assessment will include CT or MRI assessments of abdomen and pelvis for all patients. Follow-up chest CT will be performed (in those patients with thoracic lesions or upper abdomen lymphadenopathy identified at baseline assessment). Any other sites at which new disease is suspected should also be appropriately imaged. Patients must be followed until RECIST disease progression. If an unscheduled assessment was performed and the patient has not progressed, every attempt should be made to perform the subsequent assessments at their scheduled visits. Following disease progression further RECIST assessments will not be performed and assessment of disease will be as per local clinical practice.

b All anti-cancer treatments (including, but not limited to, chemotherapy and targeted agents), and the Investigators opinion of response to them and the date of progression need to be recorded.

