## Efficacy assessments

### CT and MRI scans tumour assessments (Modified RECIST 1.1)

Following the baseline assessment, subsequent tumour assessments according to modified RECIST 1.1 should be performed every 12 weeks (±1week) for the first 72 weeks and then every 24 weeks (± 1 week) thereafter, relative to the date of enrolment, up to objective disease progression by RECIST.

For those patients with no evidence of disease at baseline, following a clinical complete response to chemotherapy, progression is defined by the detection of new lesions on follow up radiological assessments (modified RECIST 1.1).

The imaging modalities used for RECIST assessment will be CT or MRI scans of the neck, chest, abdomen and pelvis with other regions as clinically indicated for the assessment of disease. Any other sites at which new disease is suspected should also be appropriately imaged. The methods of assessment of tumour burden used at baseline must be used at each subsequent follow-up assessment.

Radiological examinations performed in the conduct of this study should be retained at site as source data.

All treatment decisions will be based on site assessment of scans.

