### Tumour Evaluation

RECIST 1.1 criteria will be used to assess patient response to treatment by determining progression free survival (PFS) times according to the RECIST 1.1 guideline (Eisenhauer et al 2009).

The methods of assessment of tumour burden used at baseline CT or MRI scans of neck, chest, abdomen and pelvis must be used at each subsequent follow-up assessment. Any other areas of disease involvement should be additionally imaged based on the signs and symptoms of individual patients.

Following the baseline assessment, efficacy for all patients will be assessed by objective tumour assessments every 12 weeks after enrolment, up to 72 weeks, then every 24 weeks until objective disease progression as defined by RECIST 1.1. Any other sites at which new disease is suspected should also be appropriately imaged.

If a patient discontinues treatment (and/or receives a subsequent cancer therapy) prior to progression then the patient should still continue to be followed until objective disease progression as defined by RECIST 1.1.

Categorisation of objective tumour response assessment will be based on the RECIST 1.1 criteria of response: CR (complete response), PR (partial response), SD (stable disease) and PD (progression of disease). Target lesion (TL) progression will be calculated in comparison to when the tumour burden was at a minimum (i.e. smallest sum of diameters previously recorded on study). In the absence of progression, tumour response (CR, PR, SD) will be calculated in comparison to the baseline tumour measurements obtained before starting treatment.

For patients with non-measurable disease only at baseline, categorisation of objective tumour response assessment will be based on the RECIST 1.1 criteria of response: CR (complete response), PD (progression of disease) and Non CR/Non PD.

If the Investigator is in doubt as to whether progression has occurred, particularly with response to NTL (non-target lesion) or the appearance of a new lesion, it is advisable to continue treatment until the next scheduled assessment or sooner if clinically indicated and reassess the patient’s status. If repeat scans confirm progression, then the date of the initial scan should be declared as the date of progression.

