## Sample size estimate

The sample size of approximately 220 patients is driven by the need to enrol an adequate number of patients to help understand the efficacy and safety of olaparib with the tablet formulation. Around 46 patients with BRCAm ovarian cancer will be enrolled assuming that BRCA mutation rate is 21%.

The primary analysis will be performed after the accumulation of 132 progression or death events which corresponds to 60% maturity. Assuming a median PFS value of 8.4 months, 132 PFS events will provide a 95% confidence interval of (7.1 m, 10.0 m) for the median PFS. Assuming a median PFS of 19.1 months in the BRCA mutated patients, 27 PFS events (60% of 46 BRCA mutated patients) will provide a 95% confidence interval of (13.1 m, 27.9 m) for the median PFS.

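### The protocol states two scan schedules after week 72, and its two-missed-visit censoring window fits only one of them; late PFS, mainly the updated BRCAm median, depends on which was followed

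*Protocol*

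**What the plan says.** Two overview passages give one interval with no change over time. The synopsis, in the text below the flow chart, has patients scanned "every 12 weeks relative to date of enrolment, until objective radiological disease progression as determined by the investigator". Section 1.5 of the protocol body says "at baseline and every 12 weeks relative to date of enrolment, until objective radiological disease progression as determined by the investigator". Both introduce the requirement with the word must.

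Four passages lengthen the interval after week 72:

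- Section 5.1.1: "every 12 weeks (±1week) for the first 72 weeks and then every 24 weeks (± 1 week) thereafter, relative to the date of enrolment"
- Section 5.1.2: "every 12 weeks after enrolment, up to 72 weeks, then every 24 weeks until objective disease progression as defined by RECIST 1.1"
- Table 2, footnote f: "up to 72 weeks, then every 24 weeks relative to date of enrolment"
- Table 3, footnote a: "every 12 weeks (±1 week), up to 72 weeks, then every 24 weeks (±1 week) relative to date of enrolment"

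Table 2 carries both forms. Its column header allows 12 or 24 weeks. Its tumour assessment cell says 12 weeks and points to footnote f.

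On the analysis side, Section 8.4.2 dates PFS by the scan, not the visit. It censors a patient who progresses or dies after two or more missed visits, and equates two missed visits with more than 26 weeks since the previous RECIST assessment. Section 8.5.1 uses all scans, scheduled or not, and promises updated PFS results at the final analysis. BRCAm PFS is the first-listed secondary objective. Section 8.2 plans it by "Assuming a median PFS of 19.1 months in the BRCA mutated patients, 27 PFS events" among about 46 patients.

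**The concern.** Progression that is found at a scheduled scan takes the date of that scan, so the interval between scans is part of the measured PFS. In a randomised trial the same delay would apply to both arms. This study has one arm and reports the median itself, so nothing absorbs it.

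The assumed BRCAm median of 19.1 months falls after week 72, in the stretch where the schedules differ. The same patients could therefore give different BRCAm medians and different late PFS rates, including the planned 24-month rate, depending on which passage was followed. The censoring rule adds a second problem: applied to 24-weekly scans, its wording and its figure in weeks give different answers for the same patient.

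**Working it through.** **1. The plan's own intervals.** They follow from median × exp(±1.96/√events).

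- BRCAm: 1.96/√27 = 0.377, so 19.1 × exp(±0.377) = 13.10 to 27.85 months (stated 13.1 to 27.9).
- Overall: 1.96/√132 = 0.171, so 8.4 × exp(±0.171) = 7.08 to 9.96 months (stated 7.1 to 10.0).

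Both reproduce. Neither allows for the scan interval.

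**2. Months to weeks.** Weeks = months × 30.4375/7.

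- Planning medians: 19.1 months = week 83.05; 8.4 months = week 36.5.
- Stated BRCAm interval: weeks 57.0 to 121.3.
- Scan weeks: week 72 = 16.6 months, week 84 = 19.3, week 96 = 22.1.

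**3. Date each true median at the next scheduled scan.**

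| True median (months) | Week | 12-weekly throughout | 24-weekly after week 72 |
| --- | --- | --- | --- |
| 8.4 | 36.5 | week 48 (11.0 m) | week 48 (11.0 m) |
| 16.0 | 69.6 | week 72 (16.6 m) | week 72 (16.6 m) |
| 18.0 | 78.3 | week 84 (19.3 m) | week 96 (22.1 m) |
| 19.1 | 83.05 | week 84 (19.3 m) | week 96 (22.1 m) |
| 20.0 | 87.0 | week 96 (22.1 m) | week 96 (22.1 m) |
| 23.0 | 100.0 | week 108 (24.8 m) | week 120 (27.6 m) |

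The schedules disagree by 12 weeks (2.8 months) for a true median in weeks 72 to 84, 96 to 108 and so on. They agree in weeks 84 to 96. The planning value lies about one week inside the first differing range.

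**4. Sampling error with 46 patients.** Simulation: exponential PFS with median 19.1 months, ±1-week scan windows, cut-off at the 27th BRCAm event, 1,500 runs. Uniform accrual over 30 weeks is an assumption.

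- The typical reported median was 19.4 months (12-weekly) against 22.0 months (24-weekly).
- The average shift was 1.1 months. About 40% of runs shifted by more than 2 months, and the rest by less than 1 month.
- If unscheduled scans catch 30% or 50% of progressions at once (assumed shares), the average shift is 0.7 or 0.5 months.
- With about 60 months of follow-up the average is again about 1.1 months, with about 41% of runs shifted by more than 2 months.

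**5. The 132-event cut-off.** The schedules first differ at week 84. For an exponential with median 8.4 months, 60% of events are reached at 8.4 × ln(2.5)/ln(2) = 11.1 months of follow-up, before any detection delay. Simulation with accrual over 3 to 9 months (assumed) gives mean follow-up of about 13 months and a longest follow-up of about week 61 to 76. Almost nobody has reached week 84, so the shift is about zero.

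The synopsis calendar is slower. It expects enrolment from Q2 to Q4 2018 and the 132nd event in Q2 2020, roughly 18 to 24 months later (weeks 78 to 104). On that calendar, part of the shift could already appear at the primary analysis.

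**6. The censoring window.** 26 weeks = 2 × 12 + 2 × 1. The same construction for 24-weekly scans gives 2 × 24 + 2 × 1 = 50 weeks. Take a patient scanned at week 72 who misses week 96 and is found to have progressed at week 120. One scan is missed and 48 weeks have passed. The words (two or more missed visits) count the event; the figure (more than 26 weeks) censors it at week 72.

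**The case against.** The strongest reply is that the protocol does not have two competing schedules. The assessment sections and both schedule tables agree on the change at week 72, and Section 5.1.2 sends sites to the tables, so the synopsis and Section 1.5 may simply be abbreviated. That is plausible. However, Section 1.5 is protocol text with an unqualified requirement, and the 26-week window shows that the shorter interval also entered the analysis rules. A reader might infer that sites scanned on different schedules and mixed delays within one curve; nothing in the document shows that this happened.

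A reader might also infer that every progression between weeks 72 and 96 would be recorded at week 96, so that the BRCAm median is overstated by the full 2.8 months. The documents do not support this:

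- Unscheduled scans count, suspected new disease is imaged, and deaths need no scan.
- The full shift is a large-sample result close to the edge of a differing range. For a true median between 19.3 and 22.1 months, both schedules give week 96 in a large sample.
- The stated interval of 13.1 to 27.9 months is much wider than the shift.
- The 19.1 months is itself an investigator-assessed trial median and may already contain detection delay. The scan schedule behind it is not in the document.

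Finally, version 4.0 is dated January 2023 and last enrolment was estimated for Q4 2018, so new wording cannot change scans already done. That is right. It still settles how those scans are analysed and described.

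**Conclusion.** The contradiction stands, and so does the mismatch between the 26-week window and a 24-week interval. The numerical consequence is moderate and conditional. If the true BRCAm median is near 19.1 months, the reported median with 46 patients and mature follow-up differs by about 1.1 months on average between schedules, or 0.5 to 0.7 months with the assumed shares of unscheduled detection. This rests on exponential PFS and on scans kept within one week of schedule. The difference is systematic, so a larger sample would not remove it.

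A reader might extend this to the primary result; that is not supported. At 8.4 months both schedules date the overall median at the same scan, and under the planning medians the BRCAm shift at the 132-event cut-off is about zero. What is affected is mainly the updated BRCAm PFS at the final analysis and PFS beyond week 72. The correction should be made, but it does not put the primary objective in doubt.

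**What to change.** Reconcile the synopsis and Section 1.5 with Sections 5.1.1 and 5.1.2 and Tables 2 and 3, so that one scan schedule is stated throughout. Which schedule that should be is for the sponsor and investigators; this review does not choose. Then make the two-missed-visit window in Section 8.4.2 match that schedule after week 72, so that its wording and its figure in weeks censor the same patients. The cost is a few lines of text and, if the window changes, one adjustment to the PFS derivation.

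Optionally, report an interval-censored (Turnbull) estimate of the BRCAm median beside the Kaplan-Meier estimate. It uses scan dates already collected and costs one extra descriptive analysis. The point does not depend on it.
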